**Varenicline as Treatment for Cognitive Deficits and Cigarette Smoking in Schizophrenia – Efficacy and Predictors**

**I BRIEF BACKGROUND AND RATIONALE-SUMMARY**

Most schizophrenic patients smoke cigarettes and many are heavy smokers and are very reluctant to stop smoking. There is some experimental evidence that administering nicotine to schizophrenic patients may improve some aspects of their cognitive function. There is also literature establishing abnormalities or deficits of the α7 nicotinic receptors associated in a complex way to schizophrenia. Varenicline is an α7 nicotinic agonist and we would predict that varenicline should benefit schizophrenia by improving cognitive function. It may have some of the cognitive benefits of nicotone administration and at the same time reduce cigarette smoking. If varenicline showed cognitive enhancement properties in patients with cognitive deficits in schizophrenia, this would be an important breakthrough in improving the longer term functional outcome of many patients with this illness. This provides a strong reason for conducting a careful study to evaluate whether adding varenicline to the medication of patients who are treated with standard antipsychotic medication will significantly improve their cognitive function. We also wish to tie in any beneficial effect of this drug to the abnormalities in reelin, GAD67, and DMNT1 mRNA in schizophrenia presented in the work of Costa, Guidotti, and Davis and their collaborators.

**II RESEARCH PLAN**

***2.1 General Overview.***

This will be an 8 week parallel group placebo controlled double-blind experimental design in which cognitive function and psychopathology will be evaluated in schizophrenics (DSM IV diagnoses of schizophrenia or schizoaffective disorder). (Extension to 12 weeks at some sites including NKI site for smoking and psychopathology measures.) Patients will be tested on the MATRICS cognitive battery. Psychiatric status will be evaluated with the PANSS scale. Depression and any emerging suicidal ideation will be assessed by the CALGARY Depression scale. Negative symptoms for alogia and anhedonia will be assessed at beginning and end by abbreviated sections of the SANS scale. Changes in methylating enzyme functions related to GABAergic function will be assessed by measuring DNMT1 and GAD67 mRNAs in lymphocytes. These measures will be correlated with cognitive changes produced by varenicline. Because many schizophrenic patients are chronic cigarette smokers, and varenicline also affects cigarette smoking, cigarette smoking will be monitored by smoking questionnaires and nicotine and cotinine in plasma.

***2.2 Patients***

***Number of Patients***. Up to 100 patients will be enrolled in the study and we expect a 10-20% drop out rate. Valid cases for analysis of each variable will be considered subjects who have completed at least 1 post-baseline evaluation on that variable.

***Inclusion Criteria***: Patients will be male or female, 18-65 years of age, with a DSM-IV diagnosis of schizophrenia or schizoaffective disorder determined by best estimate diagnostic approach using research DSM-IV criteria diagnostic checklist, review of chart history and data from structured interviews. Patients will be currently treated with antipsychotic medications, and be judged to have a clinically stable symptom picture and not currently in actue exacerbation of their psychotic symptoms. Patients will have a minimal level of cognitive impairment; defined by a total score of ≤90 on the Repeatable Battery for the Assessment of Neuropsychological Status [RBANS] (The total score for normal subjects is mean±sd 100±15). All schizophrenic patients will either be current cigarette smokers or patients who were regular cigarette smokers in the past, and are not currently smoking daily because they are hospitalized in a non-smoking facility.

***Exclusion criteria***: Subjects will be excluded if they have a total PANSS score>80, have a PANSS depression item score >5, have a Calgary Depression score >20, have expressed definite suicidal ideation in the last month, or have made a documented suicide attempt or clinically serious documented suicide gesture in the last year. Subjects who have a history of multiple serious suicide attempts or clinically serious gestures in the past will be excluded. Subjects who meet DSM-IV criteria for current cocaine-crack, PCP, or methamphetamine abuse in the last month will be excluded. Patients who are currently smoking marijuana will be excluded. Patients with a current neurological CNS disorder such as seizure disorder or stroke in the last year, who are currently receiving medications specifically for these conditions, will be excluded. Patients with history of possible Downs syndrome, severe mental retardation, or dementia will be excluded. Subjects who have significant renal impairment (creatinine ≥ 1.5) will be excluded. Patients with acute exacerbations of their psychosis in the last month which are judged to be clinically significant, and have not re-stabilized, will be excluded. Patients with a documented history of a myocardial infarct, documented history of atrial arrhythmias or fibrillation within the last year, or a documented medical history of thromboembolic events will be excluded. Subjects who are currently treated with varenicline, at time of screening for the study, will not be enrolled in the study.

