***2.12 Cigarette Smoking Assessments***

Since smoking is highly prevalent in schizophrenic patients, varenicline has been shown to have antismoking effects in normals and in our preliminary studies also in schizophrenic patients], and it is also possible that nicotine itself has some cognitive effects, we will assess the degree of cigarette smoking in our subjects. Some e Measures will be taken at baseline and last month of study, and others at baseline 4, 8 weeks, and last month of study.

***A). Cigarette Dependence***. To measure at baseline the degree of dependence in current cigarette smokers, we will use the *Cigarette Dependence Scale* (Ettner et al 2003), in an interviewer-administered version.

***B).*** ***Self-report interview assessment***. Self-report of number of cigarettes smoked per day over the last week. Measurements will be made at baseline, 4 weeks, and end of study

***C) Smoking Urges***- A short version Tiffany Smoking urges scale (Cox, Tiffany, Chirsten 2001)

***D)*** ***Nicotine and Cotinine in plasma***. Measurements of plasma nicotine and cotinine will be made in plasma using samples at baseline, week 4 and week 8. It with be analyzed in the Analytical Psychopharmacology Laboratory ([name], director).

*Nicotine and Cotinine Assay*

Nicotine and cotinine are assayed in plasma in the Analytical Chemistry Laboratory at the Nathan Kline Institute for Psychiatric Research, director [name]. The assay is a GC/MS assay, following the procedure described in Davis (Davis1986) with modifications for GC/MS detection. The method involves liquid/liquid extraction with N - ethyl nornicotine and Nicotine D4 and Cotinine D3 as internal standards. Separation is achieved via gas chromatography with a Restek RtX-5 amine 15m 0.25ID 0.50 um df, crossbond 5% diphenyl 95% dimethylpolysiloxane column. Nicotine is run in PCI mode; target ion 163, cotinine is run in EI mode, target ion 98. The detection limit of accurate quantification of nicotine with this assay is 3 ng/ml with intra- and inter-coefficients of variation of 4.7 and 5.9%. Cotinine limit of detection is 5 ng/ml with intra- and inter-assay coefficient of variation of 3.4% and 5.2%.

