**III STATISTICAL ANALYSIS**

***3.1 General***

The primary dependent outcome variable, will be the average score on all tests of MATRICs battery (converted to T scores from different tests). Secondary cognitive analysis will be the of the hypothesized effects of attention-vigilance, verbal memory, and visual spatial memory. Secondary outcome variables will be cigarette smoking variables( cigarettes smoked, CO, nicotine and cotinine in plasma, smoking scores, Calgary depression scores).The general analysis approach will use a repeated measures analysis of variance. If there are appreciable missing data on measures with several ( >2) sequential testings a mixed model analysis will be used. If the data deviates significantly from normality, a non-parametric approach may be utilized using Wilcoxon matched pair’s signed-ranks, or Friedman’s two way analysis of variance. To examine whether there are differences in effects in patients with different degrees of cigarette smoking, we will compare smoking measures in patients assigned to placebo or active drug, and correlate effects on neuropsychological test changes with the smoking measures described above. Paired T-tests, or repeated measures ANOVA, will be used to analyze differences in the biochemical measures. Pearson or Spearman correlations will be used to examine the relationship between baseline neurochemical measures to cognitive tests performed at baseline, and both baseline neurochemical measure and change in these measures will be correlated with change in neuropsychological test scores. Additional analyses may use these neurochemical measures or changes during treatment as a covariate in an overall repeated measures analysis of variance.

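### The smoking outcomes are compared in all patients, including inpatients with little or no smoking to reduce, so the estimated effect is diluted by an unknown amount; CO is named as an outcome but never scheduled

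*Protocol*

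**What the plan says.** **Who is admitted.** Protocol section 2.2 states: "All schizophrenic patients will either be current cigarette smokers or patients who were regular cigarette smokers in the past". The second group is further described as those who "are not currently smoking daily because they are hospitalized in a non-smoking facility". The section on subject payments distinguishes inpatients from outpatients, so both settings are part of the sample.

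**Who is analysed.** Section 2.2 also fixes the analysis set: "Valid cases for analysis of each variable will be considered subjects who have completed at least 1 post-baseline evaluation on that variable". Smoking status plays no part in it.

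**What is compared.** Section 3.1 lists the secondary outcomes as "cigarette smoking variables( cigarettes smoked, CO, nicotine and cotinine in plasma, smoking scores, Calgary depression scores", and adds that "we will compare smoking measures in patients assigned to placebo or active drug". It describes no smoker-only set and no adjustment or stratification for baseline smoking or inpatient status. Only the Cigarette Dependence Scale (section 2.12 A, Cigarette Smoking Assessments) is tied to current smokers.

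**What is measured.** Section 2.1 says that "cigarette smoking will be monitored by smoking questionnaires and nicotine and cotinine in plasma". Section 2.12 lists dependence, self-reported cigarettes per day, urges, and plasma nicotine and cotinine. For cigarettes per day it says: "Measurements will be made at baseline, 4 weeks, and end of study".

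**The concern.** Reduction of smoking is in the trial's title and rationale. A patient who is not smoking daily because of the ward enters with cigarettes per day, nicotine and cotinine at or near the floor. Neither arm can lower those values much. Averaging such patients with smokers gives a mean difference that understates the effect in smokers. It also changes with the proportion of inpatients each site happens to enrol. A reader of the results could take a diluted figure for the drug's effect on smokers.

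Separately, an outcome that is named but never scheduled cannot be analysed, and a count promised at week 4 but absent from that visit's list may not be collected.

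**Working it through.** **The plan's own figure.** There is none for smoking. Section 3.2 concerns the cognitive outcome and gives no standard deviation, so its group sizes cannot be reproduced. Its 29 per group at 80% power corresponds to a standardised difference of about 0.75 (two-sided 5%). That value is borrowed below only as a scale.

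**Inputs**
- 30 patients per arm: section 3.2.
- f, the share of patients with essentially no smoking to reduce: not in the protocol; assumed 0.10, 0.25 and 0.50.
- d, the standardised effect in smokers: assumed 0.75, with SD 1 and no mean change in smokers on placebo.

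**Step 1: dilution.** If the ward group has a fraction r of the smokers' effect, the all-patient difference is d × [1 - f(1 - r)]. The extreme is r = 0, which gives d × (1 - f). With f = 0.25, r = 0 gives a factor of 0.75. An assumed r = 0.2 gives 1 - 0.25 × 0.8 = 0.80.

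**Step 2: power in the extreme case.** Power = Φ(Δ / [SD × √(2/n)] - 1.96).

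With change fixed at zero in the share f, the variances are (1 - f) + f(1 - f)d² on active drug and (1 - f) on placebo.

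Worked for f = 0.25:
- Δ = 0.75 × 0.75 = 0.5625.
- Variances are 0.75 + 0.1875 × 0.5625 = 0.8555 and 0.75. Their mean is 0.8027, so SD = 0.896.
- All patients: 0.5625 / (0.896 × 0.2582) - 1.96 = 0.47, power 68%. With SD left at 1, power is 59%.
- Smokers only, n = 30 × 0.75 = 22.5 per arm: 0.75 / √(2/22.5) - 1.96 = 0.56, power 71%.

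| f | All-patient effect relative to smokers | Power, all patients (SD unchanged to fixed zeros) | Smokers per arm | Power, smokers only |
|---|---|---|---|---|
| 0 | 1.00 | 83% | 30 | 83% |
| 0.10 | 0.90 | 74-78% | 27 | 79% |
| 0.25 | 0.75 | 59-68% | 22.5 | 71% |
| 0.50 | 0.50 | 31-48% | 15 | 54% |

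A second illustration is in cigarettes: assumed changes of -7 and -2 per day, SD 7 in smokers, 30 per arm. The difference of 5 becomes 3.75 at f = 0.25 and 2.5 at f = 0.50. Power in all patients against smokers only is about 60% against 64%, and 40% against 47%. At f = 0.10 it is 71% against 73%.

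The size of the estimate is therefore affected much more than power. Most of the power lost relative to f = 0 comes from having fewer smokers, and no choice of analysis set restores that.

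**Step 3: measures side by side**

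| Item | Section 3.1 | Section 2.1 | Section 2.12 (smoking) | Section 2.10 |
|---|---|---|---|---|
| CO | named outcome | absent | absent | absent |
| Cigarettes per day at week 4 | cigarettes smoked named, no visit given | questionnaires, no visit given | required (item B) | not in the week 4, 8 list (item F), which has the plasma sample and urges scale |

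The weekly interview (section 2.10 D) does not list a cigarette count either.

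**The case against.** The strongest reply is that comparing the arms in everyone enrolled is a legitimate comparison for the admitted population; it answers a different question from the effect in smokers. That stands, and a reader who inferred that the analysis is invalid would go too far. The outcomes are secondary, and the MATRICS comparison is untouched.

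A reader might also infer that these inpatients cannot smoke, so that their values are zero at every visit in both arms. The protocol says only that they are not smoking daily. Occasional smoking, or discharge during the study, is not ruled out, so (1-f) is the extreme of the dilution. A share as high as one half has no support in the text either.

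It is likewise tempting to say that a pile-up at zero breaks the normal-theory tests and forces the non-parametric fallback in section 3.1. No error rate has been calculated to show this, and section 3.1 only permits that fallback.

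Finally, a smoker subset could be left to an analysis plan that is not shown, and the valid-case rule is mainly a minimum-data rule. This has some weight. But the protocol does fix the set for each variable without regard to smoking. Section 3.1 shows interest in degrees of smoking, but its method is an arm comparison plus correlations with cognitive change, which does not isolate the effect in smokers.

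**Conclusion.** The concern holds in a limited form. As written, the comparison of cigarettes per day, nicotine and cotinine mixes smokers with inpatients who have little to reduce. The estimated mean effect is diluted relative to that in smokers, by up to the factor (1-f), and varies with the inpatient mix. With f unknown, the shrinkage is at most 10% at f = 0.10 and 50% at f = 0.50. This assumes that the effect in the ward group lies between none and that in smokers. The power difference between the two sets is small on the assumed inputs. Urges can still change in abstinent inpatients, so the floor argument does not apply to them. The CO and week-4 mismatches are plain inconsistencies that do not depend on f.

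**What to change.** - For cigarettes per day, nicotine and cotinine, define the main analysis set as patients smoking at baseline: baseline self-report of smoking and baseline cotinine at or above the 5 ng/ml limit in section 2.12 D. Because the set uses baseline data only, the between-arm comparison is preserved.
- Adjust these analyses for the baseline value.
- Report the ward-abstinent inpatients and the all-patient result separately. Keep smoking urges in all patients.
- Reconcile CO: remove it from section 3.1, or add it to sections 2.12 and 2.10.
- Reconcile the week-4 cigarette count in section 2.12 B with item F of section 2.10.

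The cost is mostly wording. The baseline smoking questionnaire and plasma sample are already scheduled (section 2.10 C). Scheduling CO, or adding the week-4 count to item F, would add a small data-collection burden. The smoking analysis will have fewer patients. Power should be about equal or slightly higher if abstinent patients change little; that is not shown if many of them smoke intermittently.

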***2.3 Antipsychotic and Other Medication***

Patients will be treated with stable antipsychotic medication. They may be treated with accessory psychotropic medication (mood stabilizers, antidepressants, antianxiety agents, antiparkinson agents) if these medications have been regularly prescribed for at least 2 weeks before any study cognitive tests is performed. Prn doses of antipsychotic drugs are permitted they will be maintained on current drugs they are receiving which are used to treat medical conditions. Psychotropic and medical drugs will remain stable during the course of the study except for clinical conditions or serious emergent side-effects indicate that a change is immediately needed for clinical care.

***2.4 Study Medication***

After baseline evaluation the patient will receive study medication, active or placebo varenicline, for a period of 12 weeks. Varenicline will be administered in a dose of 0.5 mg - 1.0 mg/day for the first week, and 2.0 mg/day dose (two 1 mg tablets) for the remainder of the study period. If the patient experiences persistent nausea or other side-effects which he does not become tolerant to over the course of 2-3 weeks to the dose can be reduced to 1 mg/day.

***2.5 Psychiatric Evaluations***

Patients will be evaluated with PANSS rating scale, Calgary Depression Scale at baseline, and then monthly and end of study. The modified SANS scale will be administered at baseline and end of study. Patients will be seen and evaluated with a brief interview at least weekly by research staff team. If the patient’s psychiatric status appears to be significantly worsening, or if he expresses a clinically significant increase in depression or suicidal ideation, a PANSS, and Calgary Depression scale will be repeated more frequently.

***2.6 Cognitive evaluations***

A) The patient will be evaluated with the RBANS to see if he qualifies on cognitive scores as defined in inclusion criteria. He will be given a brief trial on the Matrix mazes to reduced practice effects on this test.

B) Patients who qualify on the basis of RBANS scores will be administered the MATRICS Cognitive battery at baseline and last month of study. The MATRICS Battery is an expert consensus cognitive battery which has been developed to be used in studies of psychoactive drugs that may benefit cognition in schizophrenia. The Social Cognition MSCEIT will be excluded because of previously documented difficulty in administering this to seriously ill schizophrenic patients and questions about its usefulness and validity.

C) At the U.S. sites another measure of spatial memory was added, and computer navigation task ( 'water task') which is a human analogue of a spatial memory task sued in many animal studies.

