***2.9 Neurochemical Measurements***

DNMT, TET, Glucorticoid receptor, BDNF, and related mRNA's will be assessed in lymphocyte samples draw at b baseline and week 8 of study.

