***2.10 Outline of Research Evaluation Schedule***

A) Pre- consent screening -Screening-Chart review of medical and psychiatric diagnosis, and psychopathology and behavior.

*B) Consent*- RBANS, PANSS, CALGARY DEPRESSION, Modified SANS Scale, smoking surges scales

*C)Baseline*- MATRICS Cognitive Battery, Cigarette Dependence Scale, Current Smoking questionnaire, Plasma Sample for Nicotine-Cotinine, Blood Sample for determination of α7 mRNA and DNMT1 and GAD67 mRNA’s in lymphocytes .Side-effect checklist.

DNA Sample may be collected at baseline or any later point if the subject consents to this additional procedure.

*D)Weekly*- weekly interview, with questioning of major changes in psychiatric status or side effects, drug distribution, counting of pills from previous week.

*E)Week 2*- side-effects checklist

*F)Week 4,8*- PANSS, Calgary Depression Scale, side effects checklist, nicotine-cotinine sample, smoking urges scale, side-effects checklist.

*G)Week 8-12* -PANSS, Calgary Depression Scale, side-effects checklist list, Blood Sample for determination of α7 mRNA and DNMT1 and GAD67 mRNA’s in lymphocytes, smoking urges scale , MATRICS Cognitive Battery, Modified SANS, Cigarette Dependence Scale, Current Smoking questionnaire, Plasma Sample of Nicotine Cotinine, side effects checklist.

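### The protocol gives conflicting treatment lengths and no single week for the primary MATRICS test, so the primary endpoint can fall anywhere from week 8 to week 12

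*Protocol*

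**What the plan says.** Only the protocol is at hand. It gives two treatment lengths.

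- Section 2.1 starts from 8 weeks and names cognition among what is assessed: "This will be an 8 week parallel group placebo controlled double-blind experimental design in which cognitive function and psychopathology will be evaluated". It adds a longer period for part of the trial: "Extension to 12 weeks at some sites including NKI site for smoking and psychopathology measures".
- Section 2.4 has no restriction by site: "the patient will receive study medication, active or placebo varenicline, for a period of 12 weeks".

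The primary outcome in section 3.1 is the mean T score over the MATRICS tests, with no week attached. The battery is given once at baseline and once later.

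- Section 2.6 says that qualifying patients "will be administered the MATRICS Cognitive battery at baseline and last month of study".
- Section 2.10 lists the later administration only under item G, labelled Week 8-12, whose contents include "smoking urges scale , MATRICS Cognitive Battery, Modified SANS, Cigarette Dependence Scale, Current Smoking questionnaire". Item E (week 2) and item F (weeks 4 and 8) do not list it.

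The mRNA measures, by section 2.9, "will be assessed in lymphocyte samples draw at b baseline and week 8 of study". Section 2.10 puts the follow-up lymphocyte sample in item G, Week 8-12.

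**The concern.** With one post-baseline test, the week of that test defines which treatment effect the trial estimates. Here the week depends on a study length that the protocol states in two ways and that section 2.1 allows to differ by site. If some sites test at week 8 and others at week 12, the pooled difference between arms averages two durations, in proportions set by enrolment at each site.

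Two further matters depend on the same week.

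- Section 3.1 plans to correlate change in the neurochemical measures with change in test scores. The text permits a week-8 blood sample to be paired with a week-12 test.
- Section 2.2 counts a patient as valid for a variable only with a post-baseline value on it, and expects 10-20% dropout. A week-12 test leaves up to four more weeks in which a patient can leave without a primary outcome.

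This is not a detail to leave to an analysis plan. Sites schedule visits from the protocol, and no later analysis can move a test to another week.

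**Working it through.** **1. What each section permits for the post-baseline MATRICS**

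- Section 2.1: cognition belongs to the 8-week design, and the extension is described for other measures. This points to testing by week 8.
- Section 2.4: everyone is treated for 12 weeks. No MATRICS week is given, but the final month becomes about weeks 8-12.
- Section 2.6: the final month is about weeks 4-8 of an 8-week study and about weeks 8-12 of a 12-week study.
- Section 2.10, item G: weeks 8-12.
- For the mRNA sample: week 8 (section 2.9) or weeks 8-12 (section 2.10).

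**2. Spread in time on drug under the schedule**

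- Total: 12/8 = 1.5.
- After the first-week dose step in section 2.4: (12 − 1)/(8 − 1) = 11/7 = 1.57.

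**3. Is there a week that fits?** Week 8 does. It is the end of an 8-week study, the start of the final month of a 12-week study, inside the item G range, and the mRNA week in section 2.9. But nothing tells a 12-week site to choose it. The smoking assessments section lists weeks 4 and 8 and the final month as separate occasions, and section 2.10 separates item G from the week-8 visit and puts MATRICS only in G. A 12-week site could reasonably test after week 8.

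**4. Size if the effect depends on duration (illustration; the inputs marked are assumptions)**

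Section 3.2 gives 15 or 29 per group for 80% power at α = .05 and an 18-28% improvement. It states no standard deviation, so those figures cannot be reproduced, and this point does not dispute them. With the planned 30 per group and a two-sided t-test (two-sided assumed), 80% power corresponds to a standardised difference of 0.736. Suppose this is the week-12 effect, the week-8 effect is a fraction f of it, and half the patients are tested at each week (all assumed). Then the pooled difference = 0.736 × (0.5f + 0.5).

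| f | Pooled difference | Power, half at each week | Power, all at week 8 |
|---|---|---|---|
| 1.00 | 0.736 × 1.000 = 0.74 | 80% | 80% |
| 0.90 | 0.736 × 0.950 = 0.70 | 76% | 71% |
| 0.75 | 0.736 × 0.875 = 0.64 | 69% | 56% |
| 0.67 | 0.736 × 0.835 = 0.61 | 65% | 47% |

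The last row is what linear growth to week 12 would give (8/12 = 0.67). The last column shows that the mixture is not always the least powerful option. What it lacks is a defined duration.

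**5. Added variability.** Mixing two effects in equal shares adds 0.5 × 0.5 × (difference)² to the variance in the active arm. At f = 0.67 the difference is 0.33 × 0.736 = 0.243 SD, so the addition is 0.25 × 0.243² = 0.015, about 1.5% of the outcome variance. The direct loss of precision is small, and the main harm is to interpretation.

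**The case against.** The strongest reply is that the protocol can be read without any mixture. Section 2.1 limits the extension to smoking and psychopathology, so cognition stays in the 8-week design, and testing everyone at week 8 contradicts neither section 2.6 nor item G. This stands in part: the documents do not show that the endpoint will fall at different weeks, only that it can. The reply does not remove the conflict between sections 2.1 and 2.4, nor the absence of a stated week.

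A reader might infer more than the text supports:

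- **A threefold range, 4 to 12 weeks on drug.** Section 2.6 read alone would allow a test as early as about week 4 at an 8-week site. The schedule in section 2.10 places MATRICS no earlier than week 8, so the supported spread is 1.5-fold.
- **A biased comparison.** The window is the same for active drug and placebo, so the documents show no bias between arms.
- **Loss of 8-week patients from the repeated-measures ANOVA of PANSS or smoking.** Section 3.1 provides a mixed model where a measure has more than two testings and appreciable missing data.
- **A certain mismatch of mRNA and cognition.** Item G puts the blood sample and MATRICS in one visit. They separate only if section 2.9 governs the blood and MATRICS is done later.

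**Conclusion.** The point holds as a conflict in the text and an unfixed primary time point. Under the schedule, the single post-baseline MATRICS can fall from week 8 to week 12, between sites or between patients at a site: 1.5-fold in total time on drug. The consequence is conditional. If the effect is level from week 8, the estimate and the power are unchanged. If it is still growing, the pooled estimate describes no stated duration and loses a little precision. Against a week-12 effect powered at 80%, the illustrative mixtures give about 65-76% power. Those figures rest on the assumed growth, the half-and-half split and a two-sided test, none of which the protocol states. The possible mismatch between mRNA samples and cognitive tests is a secondary consequence. Because the primary endpoint is affected and tests done in different weeks cannot be realigned afterwards, the text should be corrected.

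**What to change.** 1. Reconcile sections 2.1, 2.4, 2.6, 2.9 and 2.10 on treatment duration. Which duration stands is for the sponsor and the clinical team to decide, and this review takes no position on it.
2. In sections 2.6 and 2.10, replace the final-month wording and the Week 8-12 label for MATRICS with one week that every site reaches, with a narrow window, and state the same week with the primary outcome in section 3.1. Week 8 is compatible with sections 2.1, 2.6, 2.9 and 2.10 whichever duration stands. Week 12 would be reached by every site only if the 12-week duration is confirmed for all.
3. Draw the follow-up mRNA sample at that same visit, and make sections 2.9 and 2.10 agree.

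The cost is protocol wording and a visit-window instruction to sites. No visit or test is added.
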